## Abstract

**Background:**

Postoperative cancer recurrence is a major problem following curative surgery. In a previous retrospective study of lung cancer surgery, we reported that administration of atrial natriuretic peptide (ANP) during the perioperative period reduced postoperative recurrence. We demonstrated that ANP inhibited the adhesion of cancer cells to vascular endothelium as a vasoprotective action. The objective of this study is to evaluate the effects of ANP on the incidence of postoperative cancer recurrence in lung cancer surgery.

**Methods/design:**

The present study is a multicenter, randomized trial with two parallel groups of patients with lung cancer comparing surgery alone and surgery with ANP administration for 3 days during the perioperative period. A total of 500 patients will be enrolled from 10 Japanese institutions. The primary endpoint is 2-year relapse-free survival (RFS). The secondary endpoints are 2-year cancer-specific RFS, 5-year RFS, overall survival, the incidence of postoperative complications, and the completion rate of ANP treatment.

**Discussion:**

The principal question addressed in this trial is whether ANP with its vasoprotective action can reduce cancer recurrence following lung cancer surgery.

**Trial registration:**

UMIN Clinical Trials Registry identifier: UMIN000018480. Registered on 31 July 2015.

**Electronic supplementary material:**

The online version of this article (doi:10.1186/s13063-017-1928-1) contains supplementary material, which is available to authorized users.

## Background

Cancer recurrence following curative surgery is a major problem after most cancer treatments. More than 50% of patients with resectable non-small cell lung cancer (NSCLC) will have recurrence after curative surgery [1]. Although complete surgical resection is currently considered the best option for cure in patients with most solid tumors, it is possible that surgical trauma itself influences the development of early recurrence [2–4]. First, handling of the tumor during resection can provoke detachment of tumor cells, and the amount of circulating tumor cells is enhanced during resection of the primary tumor [5, 6]. We previously reported that the presence of circulating tumor cells in the pulmonary vein during lung cancer surgery could be a prognostic indicator for early cancer recurrence [7]. Second, surgical trauma provokes a severe inflammatory reaction. There is emerging evidence to suggest that systemic inflammation can accelerate the adhesion of circulating tumor cells to the vascular endothelium of distant organs, which is a first step during extravasation in hematogenous metastasis [8, 9]. Although most circulating tumor cells disappear rapidly [10], it is possible that residual cancer cells could attach more efficiently to the vascular endothelium by the release of inflammatory cytokines during the perioperative period [8, 9]. Because no prophylactic strategy for cancer recurrence during the perioperative period has been established, the development of effective treatment is desirable.

We identified human atrial natriuretic peptide (ANP) as a diuretic/natriuretic and vasodilating hormone in 1984 [11]. ANP binds specifically to the guanylyl cyclase A receptor and has biological functions, including diuresis and inhibition of the renin-angiotensin-aldosterone system, as well as anti-inflammatory and antifibrotic actions [12, 13]. In the clinical setting, ANP has been used to treat patients with acute heart failure in Japan since 1995. We have previously reported that the perioperative administration of ANP had a prophylactic effect on postoperative cardiopulmonary complications by attenuating the operation-induced inflammation in patients who underwent curative surgery for lung cancer [14–16]. Recently, we showed that cancer recurrence after curative surgery was significantly lower in ANP-treated patients than in control patients (surgery alone) [17]. We found that ANP inhibited the adhesion of cancer cells to vascular endothelium by suppressing E-selectin expression induced by inflammation [17]. On the basis of our previous findings, we planned a multicenter, phase II randomized controlled trial to confirm the effects of ANP on preventing postoperative recurrence following lung cancer surgery.

## Methods/design

### Purpose

The purpose of the present study is to evaluate the effects of ANP on reducing postoperative cancer recurrence in patients with lung cancer undergoing curative surgery.

### Study setting

The study is an investigator-initiated, multi-institutional, two-arm, open-label, phase II randomized trial. The flowchart of the trial is shown in Fig. 1. The Standard Protocol Items: Recommendations for Interventional Trials (SPIRIT) 2013 checklist is given in Additional file 1.

**Fig. 1 Fig1:**
[figure not shown]
Consolidated Standards of Reporting Trials (CONSORT) flowchart. *ANP* Atrial natriuretic peptide

### Endpoints

The primary endpoint of this study is the 2-year relapse-free survival (RFS) rate after curative surgery for lung cancer. The secondary endpoints are 2-year cancer-specific RFS, 5-year RFS, 5-year overall survival, the rate of patients who complete ANP treatment, and the incidence of postoperative complications.

### Patient selection

The tumors are staged according to the seventh edition of the Union for International Cancer Control *TNM Classification of Malignant Tumours* [18, 19]. Inclusion criteria are as follows:NSCLC is suspected.Radiologically diagnosed invasive lung tumor with a consolidation/tumor ratio >0.25 is visualized by thin-section computed tomography (CT).Complete resection including mediastinal lymph node dissection is planned.Patients must not have synchronous or metachronous (within 5 years) malignancies, except for carcinoma in situ or mucosal tumors curatively treated with local therapy.Patients must be aged 20 years or older.Eastern Cooperative Oncology Group performance status must be 0–2.Organ function must be sufficient (leukocyte count ≥1500/ml, platelet count ≥1.0 × 10^5^/ml, hemoglobin ≥8.0 g/dl, total bilirubin ≤1.5 mg/dl, aspartate aminotransferase ≤100 IU/L, alanine aminotransferase ≤100 IU/L, peripheral arterial oxygen saturation on room air ≥92%).Written informed consent is provided by the patient.

### Exclusion criteria

The exclusion criteria are as follows:Dominant pure ground-glass opacity (GGO) lesion (radiological noninvasive lung tumor with consolidation/tumor ratio ≤0.25 visualized by thin-section CT)Active concurrent malignant diseasesPregnant, lactating, or potentially pregnantMental disorders that may affect the ability or willingness to provide informed consent or abide by the study protocolSystemic steroids or immunosuppressive agent medicationUncontrollable infectious disease, autoimmune disease, or other severe comorbiditiesHistory of right ventricular infarctionSevere hypotensionInappropriate for enrollment based on the judgment of the investigator

### Registration

Eligible patients are registered and randomly assigned to either the surgery with ANP group or the surgery-alone group by the covariate-adaptive randomization method (Pocock-Simon procedure) including sex (male/female), age (<70/≥70 years), clinical stage (IA/IB/≥II), CT findings (including GGO/not including GGO), and institution as covariates and strata. The randomization ratio is 1:1. Both patients and investigators are open to treatment allocation. The Clinical Study Data Collecting System is used for patient registration and randomization, and the Research Electronic Data Capture (REDCap™) system is used for data management. Enrollment was started in September 2015 and scheduled to continue for 2 years.

### Treatment methods

Treatment flow is shown in Fig. 1. The patients enrolled in this study receive surgery alone or surgery with ANP (group A, curative surgery with ANP; group B, curative surgery alone).

In both groups, the surgical procedures undertaken include segmentectomy, lobectomy, or pneumonectomy with systematic node dissection in open thoracotomy or video-assisted thoracic surgery. Standard systematic node dissection (ND2) includes complete removal of the hilar and mediastinal nodes.

In group A, human ANP (Daiichi-Sankyo Pharmaceutical Inc., Tokyo, Japan) is continuously infused intravenously at 0.025 μg∙kg^−1^∙minute^−1^ for 72 h beginning more than 2 h before the start of surgery. In group B, there is no agent used in addition to curative surgery. The protocol treatment is to be stopped if curative surgery is not performed.

### Follow-up

After curative resection, the information regarding postoperative complications within 30 days following surgery is recorded and sent to the data center. The incidence of postoperative complications is one of the secondary endpoints. All patients are followed with scheduled examinations, including a physical examination, serum biochemistry testing, chest x-ray, contrast-enhanced chest and abdominal CT, contrast-enhanced brain magnetic resonance imaging (MRI), and bone scintigraphy to detect postoperative recurrence for 5 years. Fluorodeoxyglucose-positron emission tomography (FDG-PET) can replace bone scintigraphy. Chest and abdominal CT are performed every 6 months following surgery. Brain MRI and bone scintigraphy or FDG-PET are performed every year following surgery. The schedule of this trial is shown in Fig. 2.

**Fig. 2 Fig2:**
[figure not shown]
Schedule of enrollment, interventions, and assessments for the Japan Human Atrial Natriuretic Peptide for Lung Cancer Surgery Study. *CT* Computed tomography, *FDG-PET* Fluorodeoxyglucose-positron emission tomography, *MRI* Magnetic resonance imaging

### Radiological assessment

Radiographic reviews for the development of postoperative recurrence are performed by the independent central image reading board, which consists of three certified radio-oncologists. All board members are blinded to treatment allocation. All films, including chest and abdominal CT, brain MRI, and bone scintigraphy or FDG-PET scans, are reviewed regularly by the board.

### Statistical methods

The present study is a phase II randomized trial to evaluate the efficacy and safety of ANP administration during lung cancer surgery. This study is designed primarily to evaluate the 2-year RFS in both groups and to demonstrate whether ANP prevents postoperative recurrence within 2 years after curative surgery. In the previous study [17], the hazard ratio for the 2-year RFS was estimated to be 0.28 (95% confidence interval 0.09–0.87) in curative surgery with ANP compared with curative surgery alone. Because this previous observational study was retrospective, we conservatively assumed the hazard ratio to be 0.50 in the present study as the upper limit of the 70% confidence interval of the previous study. To evaluate the superiority of curative surgery with ANP (group A) over curative surgery alone (group B), the total sample size was calculated as 409 patients (95 events in total are expected), assuming 70% RFS in group B with 90% power at a one-sided αlevel of 2.5% using a log-rank test, assuming an expected accrual period of 2 years and a follow-up period of 2 years. A total of 500 patients will be recruited into the study, accounting for patients lost to follow-up, such as for benign tumors or incomplete resection.

Analyses will be done on the basis of the full analysis set (FAS). Based on the intention-to-treat (ITT) principle, the FAS includes all randomized subjects without major protocol violations. An ITT-based or per-protocol based analysis will be done to assess the robustness of the conclusions derived from the FAS-based analysis. Patient demographic data will be analyzed descriptively; categorical variables will be assessed with the chi-square test or Fisher’s exact test, whereas continuous variables will be assessed with Student’s *t* test or the Wilcoxon rank-sum test, as appropriate. The survival curves for 2-year RFS (primary endpoint) and the 2-year cancer-specific RFS, 5-year RFS, and overall survival (secondary endpoints) will be estimated using the Kaplan-Meier method and compared between the two groups by the log-rank test. The hazard ratio with its 95% confidence interval will be calculated using a proportional hazards model. The proportional hazards assumption will be investigated graphically, with a test based on Schoenfeld residuals. Safety data will be analyzed descriptively for the treated set, which consists of all randomized patients who receive at least one study treatment. All reported *P* values will be two-sided. The statistical analysis plan, which includes more technical and detailed elaboration of the principal features stated in the protocol, will be prepared separately and finalized before database-locking. All statistical analyses will be conducted at the data center in the National Cerebral and Cardiovascular Research Center.

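### Kaplan-Meier is fixed for 2-year cancer-specific RFS; if non-cancer deaths are censored, it slightly overstates the actual 2-year risk of relapse or cancer death

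*Protocol article*

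**What the plan says.** The Endpoints section of the protocol article lists cancer-specific RFS apart from RFS: "The secondary endpoints are 2-year cancer-specific RFS, 5-year RFS, 5-year overall survival". It does not say which events count or how deaths from other causes are handled.

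Statistical methods then treats all these endpoints alike: "The survival curves for 2-year RFS (primary endpoint) and the 2-year cancer-specific RFS, 5-year RFS, and overall survival (secondary endpoints) will be estimated" and, continuing the same sentence, "using the Kaplan-Meier method and compared between the two groups by the log-rank test". For the effect size it adds: "The hazard ratio with its 95% confidence interval will be calculated using a proportional hazards model". No competing-risk method is named. The section leaves more technical detail to a separate SAP, to be finalized before the database is locked; that SAP is not shown.

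Under Purpose, the aim is to "evaluate the effects of ANP on reducing postoperative cancer recurrence in patients with lung cancer undergoing curative surgery".

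**The concern.** If RFS is taken in its usual sense (relapse or death from any cause), cancer-specific RFS differs from it only when non-cancer deaths are not events. Under Kaplan-Meier those patients are censored at death and treated as though they could still relapse later. The complement of the curve then estimates relapse risk in a hypothetical setting without other deaths, not the share of patients who relapse or die of cancer.

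Other deaths are plausible here. The surgery includes pneumonectomy, age 70 or over is an allocation factor, and performance status up to 2 is allowed. Because the trial's purpose concerns recurrence, readers are likely to take the 2-year cancer-specific figure as an actual recurrence risk. What is at stake is that one descriptive curve and its 2-year value.

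**Working it through.** **1. The plan's own figure.** Inputs from Statistical methods and Registration: "assuming 70% RFS in group B with 90% power at a one-sided" level of 2.5%, "we conservatively assumed the hazard ratio to be 0.50 in the present study", and "The randomization ratio is 1:1".

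- Events (Freedman): (1.960 + 1.282)² × [(1 + 0.5)/(1 − 0.5)]² = 94.57, rounded up to 95.
- 2-year event probabilities: group B 0.30; group A 1 − 0.70^0.5 = 0.1633; mean 0.2317.
- N = 94.57/0.2317 = 408.2, rounded up to 409.

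The stated 409 patients and 95 events reproduce. They concern RFS and do not depend on this point.

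**2. Formulas.** Take constant cause-specific hazards, accumulated over 2 years: h for relapse or cancer death, d for non-cancer death.

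- 1 − KM (non-cancer deaths censored) = 1 − exp(−h)
- Cumulative incidence (CIF) = h/(h + d) × [1 − exp(−(h + d))]

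The first exceeds the second whenever d > 0. The documents give no non-cancer death rate, so the rates below are assumptions shown as a range.

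**3. Scenario (a): total 2-year RFS held at the design values** (B 70%, A 83.7%). Let s be the share of first events that are non-cancer deaths, equal in both arms. Then 1 − KM = 1 − S^(1−s) and CIF = (1 − s)(1 − S).

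| s | B: 1 − KM | B: CIF | B: excess (points) | A: excess (points) |
|---|---|---|---|---|
| 5% | 28.74% | 28.50% | 0.24 | 0.07 |
| 10% | 27.46% | 27.00% | 0.46 | 0.13 |
| 20% | 24.82% | 24.00% | 0.82 | 0.23 |
| 30% | 22.09% | 21.00% | 1.09 | 0.30 |
| 50% | 16.33% | 15.00% | 1.33 | 0.36 |

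**4. Scenario (b): the design values applied to cancer events alone.** Net 2-year risk is 30% in B (h = −ln 0.70 = 0.3567) and 16.33% in A (h = 0.1783). Net 2-year non-cancer mortality m is the same in both arms, with d = −ln(1 − m).

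Worked case, m = 5% (d = 0.0513):

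- B: 0.3567/0.4080 × (1 − 0.70 × 0.95) = 0.8743 × 0.335 = 29.29%
- A: 0.1783/0.2296 × (1 − 0.8367 × 0.95) = 0.7766 × 0.2052 = 15.93%

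| m | B: CIF | B: excess (points) | A: CIF | A: excess (points) | B − A by KM (points) | B − A by CIF (points) |
|---|---|---|---|---|---|---|
| 1% | 29.86% | 0.14 | 16.25% | 0.08 | 13.67 | 13.60 |
| 2% | 29.72% | 0.28 | 16.17% | 0.16 | 13.67 | 13.54 |
| 5% | 29.29% | 0.71 | 15.93% | 0.40 | 13.67 | 13.35 |
| 10% | 28.56% | 1.44 | 15.53% | 0.81 | 13.67 | 13.04 |

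**5. Unequal competing deaths.** Suppose net relapse is 25% in both arms (h = 0.2877) and non-cancer mortality is 3% in one arm and 8% in the other. 1 − KM is 25.0% in both. CIF is 0.2877/0.3181 × (1 − 0.75 × 0.97) = 24.6% in the first and 0.2877/0.3711 × (1 − 0.75 × 0.92) = 24.0% in the second. So the cumulative incidence moves with competing deaths, and the Kaplan-Meier curve does not.

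**The case against.** **A reader might infer that Kaplan-Meier would let a shift in non-cancer deaths pass for a fall in relapse,** the more so because the Background reports that ANP reduced cardiopulmonary complications. This is not supported. With non-cancer deaths censored, the curve depends only on the cause-specific relapse hazard, and step 5 shows it unchanged when competing deaths differ. The measure that shifts is the cumulative incidence. In addition, the Background report is about complications, not mortality.

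**A reader might also infer that the test or hazard ratio is wrong.** It is not. The log-rank test and proportional hazards model address the cause-specific hazard, a sound target for whether ANP reduces recurrence. The primary question rests on 2-year RFS, which, if it counts all deaths, has no competing-death problem.

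**The censoring rule is inferred.** This stands. An article may leave event definitions to the SAP, so the missing definition is not itself the complaint. The estimator, however, is stated, and an SAP that only elaborates the sentence would carry Kaplan-Meier forward.

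**The effect is small.** This also stands. With about 204 patients per arm, the standard error of the 2-year difference is √(0.30 × 0.70/204 + 0.163 × 0.837/204) = 4.1 points. The largest shift in the difference, 13.67 − 13.04 = 0.63 points, is about 0.15 of that.

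**Net risk is a legitimate estimand.** It is, but the protocol does not say that net risk is intended, and its interpretation needs relapse and other death to be independent.

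**Conclusion.** The point holds as a minor one. The protocol names Kaplan-Meier for an endpoint that, on the inferred reading, has a competing event. The complement of that curve then overstates the actual 2-year probability of relapse or cancer death. The direction is certain once any non-cancer death precedes relapse. The size is about 0.1 to 1.4 points per arm, and about 0.1 to 0.6 points in the between-arm difference under scenario (b).

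These sizes rest on constant hazards, on the RFS design values used as anchors, and on assumed non-cancer death rates. Only the descriptive curve and 2-year rate of one secondary endpoint are affected. Nothing here suggests that a conclusion of the trial would change.

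**What to change.** In Statistical methods and in the SAP:

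1. Define the events of cancer-specific RFS and state how non-cancer deaths are handled.
2. Estimate the 2-year probability of relapse or cancer death by Aalen-Johansen cumulative incidence, with non-cancer death as the competing event.
3. Keep the planned log-rank test and Cox hazard ratio, labelled as cause-specific.
4. Show the cumulative incidence of non-cancer death by arm beside them, because the cumulative incidence of relapse can itself shift if competing deaths differ between arms.

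Kaplan-Meier stays for RFS and overall survival. The cost is a change of wording before database lock and a few lines of code. The downside is a little extra analysis and two measures that must be read together.

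### The primary log-rank test and hazard ratio name none of the five minimisation factors; run as written, the test is conservative to the extent that stage and GGO are prognostic

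*Protocol article*

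**What the plan says.** The Registration section allocates patients 1:1 by minimisation, with "sex (male/female), age (<70/≥70 years), clinical stage (IA/IB/≥II), CT findings (including GGO/not including GGO), and institution as covariates and strata". The abstract gives the number of institutions as 10.

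The Statistical methods section says that the curves for 2-year RFS, the primary endpoint, and for the secondary survival endpoints "will be estimated using the Kaplan-Meier method and compared between the two groups by the log-rank test". It adds: "The hazard ratio with its 95% confidence interval will be calculated using a proportional hazards model". No stratum or covariate is named for either. The same section sizes the trial with a plain log-rank test.

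The section also announces a separate statistical analysis plan, "which includes more technical and detailed elaboration of the principal features stated in the protocol, will be prepared separately", to be final before the database is locked. That plan is not at hand.

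**The concern.** Minimisation makes the arms more alike on stage, GGO and the other factors than simple randomisation would. If those factors predict relapse, the log-rank statistic varies less from trial to trial than its usual variance formula assumes. The unstratified test then rejects a true null less often than its nominal level, and its confidence interval is wider than it needs to be. Stratifying by the prognostic factors brings the variance formula back into line with the design.

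What is at stake is some power, and precision in the hazard ratio. Timing matters too. The trial is open-label and the analysis plan need only be final before database lock, so strata chosen late could look data-driven.

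**Working it through.** **Step 1. Reproduce the plan's figure.** Inputs from Statistical methods: hazard ratio 0.50, control 2-year RFS 70%, one-sided 2.5%, power 90%.

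- Events (Freedman): (1.960 + 1.282)² × [(1 + 0.5)/(1 − 0.5)]² = 10.507 × 9 = 94.57, so 95.
- Event probability by 2 years: 0.300 in group B and 1 − 0.70^0.5 = 0.163 in group A; mean 0.2317.
- Patients: 94.57 / 0.2317 = 408.2, so 409.

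Both stated figures reproduce with an unstratified test and each patient followed for 2 years.

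**Step 2. Simulate the test after minimisation.** Taken from the protocol: 409 patients, minimisation on the five factors, 10 institutions, control 2-year RFS of 70%. All patients are censored at 2 years. Assumed, because the protocol does not give them: factor frequencies, a biased-coin probability of 0.8, institution not prognostic, and the prognostic effects. The moderate case has hazard ratio 3 for stage ≥II and 2 for tumours without GGO. The strong case has 6 and 4. Each scenario has 6,000 trials; the Monte Carlo standard error is about 0.2 points for size and 0.2–0.6 for power.

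One-sided size at nominal 2.5%:

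| Prognostic effects | Unstratified | Stratified by stage × GGO | Unstratified, simple randomisation |
|---|---|---|---|
| None | 2.4% | 2.4% | 2.2% |
| Moderate | 1.8% | 2.5% | 2.3% |
| Strong | 0.9% | 2.5% | 2.5% |

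The last column shows that the conservatism comes from minimisation followed by an analysis without the factors. As a check, the null standard deviation of the unstratified statistic was 0.938 (moderate) and 0.842 (strong). Then Φ(−1.96/0.938) = Φ(−2.09) = 1.8% and Φ(−1.96/0.842) = Φ(−2.33) = 1.0%, in line with the simulated sizes.

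**Step 3. Power.** The planned 0.50 can be read as the effect within strata. Alternatively, the overall 2-year rates can be held at the design values of 70% and 83.7% (0.70^0.5 = 0.837), which needs a within-stratum hazard ratio of 0.479 (moderate) or 0.437 (strong).

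| Scenario | Unstratified | Stage × GGO | Difference (points) |
|---|---|---|---|
| No prognostic effect | 91.1% | 90.9% | −0.2 (within simulation error) |
| Moderate, within-stratum 0.50 | 89.6% | 91.7% | 2.1 |
| Moderate, overall design rates | 92.2% | 94.0% | 1.8 |
| Strong, within-stratum 0.50 | 84.7% | 92.2% | 7.5 |
| Strong, overall design rates | 94.6% | 97.5% | 2.9 |

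A separate simulation used other moderate assumptions: stage mix 50/25/25 and control RFS 82/68/48%, which average to 0.50 × 82 + 0.25 × 68 + 0.25 × 48 = 70%. It gave size 1.9% against 2.4% and power 90.3% against 91.8%.

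**Step 4. How many factors to stratify by.** Stage × GGO gives 3 × 2 = 6 strata, about 95/6 = 16 events each. All five factors give 2 × 2 × 3 × 2 × 10 = 240 cells, about 95/240 = 0.4 events each. In the same scenarios, power with all five falls to 67–80%. The four factors without institution give 90–97%.

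**The case against.** The strongest objection is that this argues from silence. The article does not call the log-rank test unstratified or the model unadjusted. The Registration section describes the factors as covariates and strata, and strata for a test are ordinary content for an analysis plan that is not shown. A reader might infer that the sponsor has decided to ignore the minimisation factors; the text does not support that. What remains is that the primary test is named, the sample size rests on the same plain test, and the analysis plan is described as elaborating what the protocol states. The point therefore holds for the analysis as written.

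A reader might also infer that the trial is underpowered. It is not shown to be. The stated figures reproduce, and under moderate effects the unstratified test still has 89.6–92.2% power. The one figure clearly below 90% (84.7%) needs strong effects and 0.50 read as a within-stratum effect. The protocol says only "we conservatively assumed the hazard ratio to be 0.50 in the present study", alongside an overall RFS of 70%. If the overall design rates hold, unstratified power is at least 91%.

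A third inference would be that the unadjusted hazard ratio is biased because it lies nearer 1 than the within-stratum ratio. The two are different estimands, and the protocol does not say which it targets.

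Finally, using the factors is not free in every form, as the five-factor result shows. That limits the remedy but does not remove the point.

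**Conclusion.** The point holds in a limited form. The stated primary test and model name none of the minimisation factors. Run that way, the test is conservative in so far as stage and GGO are prognostic: one-sided size about 1.8% (moderate) to 0.9% (strong). Power forgone is about 2 points (moderate) to 3–7.5 points (strong), and none without prognostic effects. These sizes rest on assumed prognostic strengths, factor frequencies and coin probability; the direction does not.

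The error is on the safe side: a positive result is not undermined. Nor do the documents support saying that power is thrown away for nothing, since the moderate gain is small. The case for change is that stratifying by two factors costs essentially nothing if they prove not to be prognostic, and recovers power and the nominal level if they are.

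**What to change.** In the protocol or the analysis plan, and well before database lock:

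- Specify the primary log-rank test as stratified by clinical stage (IA/IB/≥II) and GGO (yes/no), using the values recorded at randomisation.
- Take the primary hazard ratio and its 95% confidence interval from a Cox model stratified by the same two factors, so that the P value and the interval match.
- Do not use institution as a stratum, and say so.
- State that the hazard ratio is conditional on the strata.
- Report as sensitivity analyses the unstratified test and hazard ratio, and a model also adjusted for age group and sex.

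The cost is wording only. Both factors are already recorded for every patient at randomisation, and the sample size does not change.
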